**Patient characteristics**												
Age	Medical records		X	—^a^		—^a^		—^a^		—^a^	—^a^	
Gender	Medical records		X	—^a^		—^a^		—^a^		—^a^	—^a^	
Comorbidities	Medical records		X	—^a^		—^a^		—^a^		—^a^	—^a^	
Previous shoulder surgery	Medical records		X	—^a^		—^a^		—^a^		—^a^	—^a^	
Indication for surgery	Medical records		X	—^a^		—^a^		—^a^		—^a^	—^a^	
**Outcome measures**												
Shoulder function	SPADI^b^ VAS^c^ CS^d^ ROM Strength Proprioception		X X X X X X	X X X X —^a^ —^a^		X X X X X X		X X X X X X		X X X X X X	X X X X X X	
Patient satisfaction	Self developed questionnaire		—^a^	X		X		X		X	X	
Quality of Life	SF-36^b^		X	X		X		X		X	X	
**Potential prognostic factors**												
Patient characteristics	Body weight Body length		X X	X X		X X		X X		X X	X X	
Preoperative shoulder function	ROM Strength Proprioception		X X X	X —^a^ —^a^		X X X		X X X		X X X	X X X	
Patient expectations	Self developed questionnaire		X	—^a^		—^a^		—^a^		—^a^	—^a^	
Soft tissue integrity	Surgery report		—^a^	—^a^		—^a^		—^a^		—^a^	—^a^	
Sling wear	Randomization		X	—^a^		—^a^		—^a^		—^a^	—^a^	
Psychosocial factors	Anxiety and depression (Hospital Anxiety and Depression Scale) Self-efficacy (Pain Self-Efficacy Questionnaire) Catastophizing (Pain Catastrophizing Scale)		X X X	X X X		X X X		X X X		X X X	X X X	
Lifestyle factors	Drug usage Physical activity (International Physical Activity Questionnaire – long version) Smoking behavior Sleep Alcohol use		X X X X X	X X X X X		X X X X X		X X X X X		X X X X X	X X X X X	
Physiotherapy treatment	Questionnaire		X	X		X		X		X	X	

^a^—: not applicable.

^b^outcomes used in the mixed-models analysis.

^c^VAS: Visual Analogue Scale.

^d^CS: Constant and Murley Score.

### Participant Timeline

The participant timeline is shown in Figure 1.

**Figure 1 figure1:**
[figure not shown]
Participant timeline.

### Sample Size

Considering a mixed regression model for repeated measures and using a moderate effect size that is still clinically relevant (20 points average decrease in SPADI score), inclusion of 5 covariates, confidence level (α=0.05), and desired power (90 %), the required total sample size is calculated to be 43 participants per group (Edland method, R package longpower 1.0-11) [50-52]. The SD of the SPADI measurements is set at 18, and is estimated from the SD measured in previous studies [31]. The variance of the residuals cannot be estimated from previous studies, but this variance only has a very limited effect on the sample size. It doesn’t change the result of the power calculation and is not included in this analysis. Given the expected dropout rate of approximately 12.5%, a total number of 97 patients will be needed. The power is set at 90% to minimize the chance of making a type II error.

### Statistical Methods

Statistical analyses will be performed using SAS Studio (version 9.4; SAS Institute Inc). Level of significance is set at *P*=.05. Descriptive statistics will be used to describe the patient population. Based on literature review, expert opinion and univariate analyses potential prognostic factors will be chosen as covariates. A mixed regression model for repeated measures will be used to assess both the evolution of the SPADI score and the SF-36 score within persons from baseline over time and the differences in evolution between participants. This type of model has the advantage that the assumption of sphericity can be relaxed. Sphericity will probably be violated, as both the SPADI score, and SF-36 score at baseline and at all the different time points will probably have different variances. Second, using mixed models it is not necessary to have complete datasets to produce accurate results. Multiple imputation of missing values is thus not needed. All available data of a participant can be used in the model estimation, even if people missed a visit. Another advantage is that it is possible to simultaneously examine within and between person phenomena that might contribute to change in outcome. A fourth advantage is that the correlation between observations within persons over time is adequately addressed [53]. One assumption that must be checked is normality of the residuals, using a Shapiro-Wilk test. If these residuals are not normally distributed, an appropriate transformation will be performed first, or a nonlinear mixed model will be used.

Correlation analyses will be used to search for correlations between the other outcomes measured such as CS, shoulder range of motion, shoulder muscle strength, and proprioception and the primary outcome measure, SPADI. Potential prognostic factors not included in the model will be described.

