**Methods:**

To reach the aims of this project, a prospective longitudinal study, running from January 2020 to March 2025, will be carried out with a follow-up of 48 months. Patients will be randomized based on sling wear. We will study factors such as shoulder function, patient expectations, psychosocial factors, lifestyle factors, sling wear, soft tissue integrity, and physiotherapy treatment. Test moments will take place preoperatively, at 6 weeks, 12 weeks, 6 months, 12 months, and 24 months. Descriptive statistics will be used to describe the patient population characteristics. Based on literature review, expert opinion, and univariate analyses, potential prognostic factors will be chosen as covariates. A mixed regression model for repeated measures will be used to assess both the evolution of the Shoulder Pain and Disability Index within persons from baseline over time and the differences in evolution between participants. Correlation analyses will be used to investigate associations between the other outcome measures such as the Constant and Murley Score, shoulder range of motion, shoulder muscle strength, and proprioception, and the primary outcome measure, the Shoulder Pain and Disability Index score. Potential prognostic factors not included in the model will be presented in a descriptive manner.

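### Covariates for the primary SPADI model are chosen partly by univariate tests on the same patients in whom they are then tested, so noise factors are likely to be reported as prognostic

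*Protocol article*

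**What the plan says.** Under Statistical Methods, the article gives the selection rule for the mixed models of SPADI and SF-36: "Based on literature review, expert opinion and univariate analyses potential prognostic factors will be chosen as covariates". The abstract repeats it ("expert opinion, and univariate analyses, potential prognostic factors will be chosen as covariates"). The significance level is P=.05. Factors that do not enter the model are to be described only.

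The Sample Size section assumes "inclusion of 5 covariates" and states that "the required total sample size is calculated to be 43 participants per group". That is 86 evaluable patients, raised to 97 for dropout.

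The primary objective in the Introduction is to find the factors that predict SPADI at baseline and its course over two years. The Discussion expects the answer to inform rehabilitation strategies.

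**The concern.** The univariate step looks at the outcome. A factor that happens to correlate with SPADI in these patients is more likely to enter the model, and its P value is then computed as if it had been chosen without looking. The nominal 5% no longer describes the chance that a noise factor is declared prognostic, and estimates for weak factors are centred too far from zero.

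In many trials covariates serve only to adjust a treatment comparison. Here the list of significant factors, with their estimates, is the primary result. A false entry is therefore an error in the main answer and could be carried into rehabilitation advice. The fault lies in a rule the article states, not in a detail it leaves out.

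**Working it through.** **The plan's own figures.** The article states no error rate for the selection procedure, so there is none to reproduce. The patient numbers used below are its own: 2 × 43 = 86, and 86 × 1.125 = 96.75, rounded to 97. The figure of 43 does not follow from the printed inputs. With 20 points, SD 18, two-sided 5% and 90% power, 2 × (1.96 + 1.28)² × 18² / 20² ≈ 17.0, or 18 per group after rounding and small-sample correction. That is a separate question and does not affect this point.

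**Candidates.** Counted from Patient Characteristics, Potential Prognostic Factors, Outcome Measures and Tables 1 to 3:
- medical-record variables 5, BMI 1
- range of motion 7, strength 5, proprioception 4 + 2 = 6
- expectations 1, soft tissue 1, sling 1
- psychosocial 4, lifestyle 5, physiotherapy 1

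Total: 5 + 1 + 7 + 5 + 6 + 1 + 1 + 1 + 4 + 5 + 1 = 37. Counting range of motion, strength and proprioception once each gives 37 − 18 + 3 = 22.

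**Noise factors expected to pass a univariate screen** (number of candidates × threshold):
- 37 candidates: 1.85 at P<.05, 3.7 at P<.10, 7.4 at P<.20
- 22 candidates: 1.1, 2.2 and 4.4

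**Benchmark.** Five covariates named in advance, all null: 1 − 0.95⁵ = 22.6% for at least one false positive, and 5% for each. Simulation gives 20–24%.

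**With selection.** Simulation with N = 86 (N = 97 is almost the same) and all candidates null. Candidates are screened one at a time, then tested together at .05. One outcome value per patient with least squares stands in for the mixed model. Chance of at least one false factor in the final model:

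| Rule | Pool | Correlation 0 | 0.3 | 0.5 |
|---|---|---|---|---|
| Best five by univariate P | 37 | 77–79% | 50–53% | 36% |
| Best five | 22 | 64% | 48% | not in the table's runs |
| Best five | 15 | 51% | 44% | 33% |
| Best five | 10 | 39% | 33% | 28% |
| Four fixed, one by univariate P | 37 | 79–80% | 69% | not in the table's runs |
| Four fixed, one by univariate P | 22 | 67% | 53% | not in the table's runs |
| All rules tried (best five, or P<.05/.10/.20) | 37 | 76–81% | 35–59% | not in the table's runs |
| All rules tried | 22 | 61–68% | 28–49% | not in the table's runs |

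When the best five of 37 are entered, each entered noise factor reaches P<.05 in 31–32% of cases (independent candidates) or 17–18% (correlation 0.3), against 5% without selection.

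**Effect sizes.** With three true factors among 37, N = 86 and at most five entered, the mean estimate of a true factor once entered is:
- true effect 0.15: 0.21–0.25 (× 1.4–1.65)
- true effect 0.20: 0.23–0.26 (× 1.2–1.3)
- true effect 0.30: about unbiased (× 0.98–1.01)

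False factors make up 25–65% of the significant ones.

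**A limit of these figures.** I also tried a P-value screen with candidates correlated at 0.5. There the chance of any false factor can fall to the 22% benchmark or below, because in many studies nothing passes the screen or the factors that pass duplicate one another. Even then, a noise factor that did enter was declared significant more often than 5% of the time. The range of 28–81% is therefore the spread of the tabulated settings, not a bound.

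**The case against.** The strongest reply is that univariate results are only one of three inputs. Literature and expert opinion might first cut the pool to 10 or 15, and measures taken on one shoulder are surely correlated. The excess is then smaller: 28–39% for ten candidates and 33–51% for fifteen, against about 22%. This stands as a reason to give a range. It does not remove the problem, because the article does not say how the inputs combine. If literature and experts fix four of five places and the data fill only one from a pool of 22 to 37, the chance is still 53–80%.

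It is also fair that the all-null case is a worst case, that the article's language is cautious, and that factors left out will be described. But factors in the model are still tested at P=.05 and presented as the answer to the primary objective.

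A reader might infer more than the documents support:
- That about 78% is this trial's error rate, or that noise factors are certain to be reported. That figure assumes 37 independent candidates ranked by univariate P alone.
- That all estimates are inflated. Strong effects are nearly unbiased.
- That explained variance will be misreported. The article does not say it will report it.
- That two outcomes, each with level and course, multiply the error. SF-36 is declared secondary, and no such multiple was calculated.
- That the absence of a named list, a screening threshold or a rule for which visit's value enters is itself a fault. An article may leave these to an analysis plan.

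**Conclusion.** The concern holds. The stated rule uses the outcome to choose factors and then tests them in the same 86 to 97 patients as if they had been fixed beforehand. With all candidates null, the chance of at least one false prognostic factor is about 28–81% in the settings tabulated, against about 22% for five covariates named in advance. Where the true value falls depends on facts the article does not give: the effective size of the pool, its correlation, and the weight given to univariate results. Weak effects that enter are overstated by a factor of about 1.4 to 1.65; strong effects hardly at all.

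These sizes rest on a candidate count derived from the listed measures and on a one-value-per-patient stand-in for the mixed model. They show direction and order of size, not the exact error rate of this study. Because the list of factors is the primary result, the rule should be changed before the analysis is run.

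**What to change.** Remove univariate analyses from the selection rule. Before analysis begins, lock a dated list of about five covariates chosen from literature and expert opinion. Include the randomized sling group, and enter each covariate with its interaction with time. Report all of them with estimates and confidence intervals, whatever their P values.

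Label every other factor exploratory. Alternatively, fit those factors in a penalised model and bootstrap the whole selection process, so that the validation covers the choosing as well as the fitting.

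The cost is one document and no new patients or measurements, but some factors move to exploratory status. Five fixed covariates still carry about a 22% chance of one false positive, so either adjust for multiplicity or say so in the report. The article states that analyses follow once data collection is complete. The list has to be fixed before then, because it cannot be made prospective after the outcome has been used for screening.

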### Outcome Measures

We selected the outcome measures based on the available literature and clinical expertise. Shoulder pain and shoulder function will be measured using the SPADI, which is the primary outcome measure. Quality of life measured with the SF-36, is the secondary outcome measure. Other measured outcomes are shoulder pain and function measured with the Constant and Murley Score (CS), the Visual Analogue Scale (VAS), active shoulder range of motion, shoulder muscle strength, and proprioception of the shoulder. The last outcome measure is patient satisfaction, measured with a self-developed questionnaire.

To measure shoulder pain and function, the SPADI [30] has shown a good internal consistency and test-retest reliability, with a Cronbach α of 0.94 and Intraclass Correlation Coefficient of 0.89 (95% CI 0.83-0.93). The questionnaire is divided in 2 subscales, a pain subscale with 5 statements, and a disability subscale with 8 statements. Every statement must be scored with a number between 0 and 10, with 0 being “no pain” or “no effort” and 10 being “the worst pain” or “so difficult that help is needed”. The overall SPADI score will be used and is calculated: ([sum of all statement scores]/130)×100. This self-administered questionnaire is available in Dutch, and is designed to measure pain and disability associated with shoulder pathology in different clinical settings [31].

Shoulder pain will be measured with the VAS (0-100). Patients will be asked to score the average pain they experience during rest and during shoulder movement on a drawn line of 100 mm, with answers ranging for 0-100. With 0 showing “no pain” and 100 showing “the worst pain.”
Shoulder pain and function will be measured with the CS, validated and reliable in patients with shoulder dysfunction [32,33]. We used a Dutch translation, which is not yet validated. A score will be calculated between 0-100, with 100 being a more functional patient.

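### A Shapiro-Wilk result on roughly 500 pooled residuals may move the primary SPADI analysis off the points scale, on which factors with a baseline difference can then falsely appear to predict evolution

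*Protocol article*

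**What the plan says.** The protocol article, Statistical Methods, plans a mixed regression model for repeated measures for SPADI (primary) and SF-36 (secondary). It names a single assumption check: "One assumption that must be checked is normality of the residuals, using a Shapiro-Wilk test". The consequence of failing it is stated: "If these residuals are not normally distributed, an appropriate transformation will be performed first, or a nonlinear mixed model will be used". The same section expects the variance of both scores to differ between time points and gives this as a reason for using a mixed model.

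Three other places bear on the rule:

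- The primary objective (end of the Introduction) has two parts: which factors predict SPADI at baseline, and which predict its course over two years.
- Outcome Measures defines a score that runs from 0 to 100: "The overall SPADI score will be used and is calculated" as the item sum divided by 130, times 100.
- Sample Size defines the relevant effect in points, "20 points average decrease in SPADI score", and the spread likewise: "The SD of the SPADI measurements is set at 18".

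**The concern.** A factor that predicts evolution is, in the model, a factor-by-time interaction. Whether such an interaction exists depends on the scale of the outcome. Two groups that fall by the same number of points from different starting levels run parallel in points, but not after a log or root transformation. The rule therefore lets a distributional diagnostic choose the scale on which the primary question is answered.

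The trigger is also ill suited to the purpose. A normality test on several hundred residuals picks up departures that matter little for tests of mean change. It also responds to unequal visit variances, which the model is meant to handle. At stake is the second half of the primary objective: for factors already related to baseline SPADI, a difference in level could be reported as a difference in recovery. The 20-point planning effect also has no direct counterpart on a transformed scale.

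**Working it through.** **Number of residuals.** Sample Size gives "43 participants per group (Edland method, R package longpower 1.0-11"), so 2 x 43 = 86 patients. The stated total of 97 follows from 86 x 1.125 = 96.75; dividing instead by 0.875 gives 98.3, so 99. There are six visits. The count is 86 x 6 = 516 for completers, 97 x 6 = 582 at most, and 582 x 0.875 = 509 after 12.5% loss: roughly 500. (The 43 per group is not reproduced from 20 points and SD 18 by a simple two-group formula, which gives 18 per group. That is a separate matter; here 43 serves only as a count.)

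**How readily the test rejects** (simulation at the 5% level; skewness and correlation are assumptions):

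| Residual skewness | 516 independent residuals | Conditional residuals, within-person correlation 0.5 | 86 independent residuals |
|---|---|---|---|
| 0.2 | 37% | 23% | 10% |
| 0.3 | 72% | 44% | 15% |
| 0.4 | 91% | not run | 24% |
| 0.5 | 99% | 89% | 38% |

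Data that are exactly normal at each visit, but with visit SDs assumed to range over 14-22, were rejected in 15-19% of runs; with SDs over 10-24, in 55-68%. Exactly normal but correlated data gave 11% (correlation 0.5) to 29% (correlation 0.7) on marginal residuals, and 5-6% on conditional residuals.

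**Whether inference in points needed rescue.** With 43 per group and residual skewness 0.5 and 1.0, the group-by-time test on untransformed scores had type I error of 4.9% and 5.1%.

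**What a transformation does to parallel change.** Take a fall of 30 points from 70 and from 50:

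- points: -30 and -30
- log(y+1): ln(41/71) = -0.55 and ln(21/51) = -0.89
- square root: 6.32 - 8.37 = -2.04 and 4.47 - 7.07 = -2.60

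Equal change in points becomes unequal change on both transformed scales.

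**Size with normal scores clipped to 0-100.** SD 18, 43 per group, correlation 0.5, mean paths from 65 down to 25 or to 18 (paths and correlation assumed), parallel in points before clipping. Rate of a significant group-by-time test when the transformation is always applied:

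| Baseline difference | Points | Log(y+1) | Root | Logit |
|---|---|---|---|---|
| 0 | about 5% | 4-5% | 4-5% | 4-5% |
| 10 | 5-6% | 39-43% | 19-21% | 11-14% |
| 20 | 7-11% | 97-98% | 69-77% | 32-46% |

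The rise to 11% in points occurs where the floor at 0 makes the observed scores themselves non-parallel.

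**Size when the rule itself is followed.** The previous table does not ask whether the test would fire or whether the transformation would help. The relevant joint event is: Shapiro-Wilk rejects in points, the transformation improves the Shapiro-Wilk W statistic, and the factor-by-time test is falsely significant. For a factor with a constant 10-point effect:

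- Clipped-normal scores: log improved W in 0% of runs and root in 2-8%. The joint rate was 0% for log and at most 3% for root.
- Right-skewed postoperative scores (assumed): the test rejected in 97-100% of runs, root improved W in all runs and log in 63-96%. The joint rate was 23-67% for root and 47-94% for log, against 5-6% for the analysis in points.

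**The case against.** The strongest reply is that the rule asks for a transformation that is suitable, and only to cure non-normal residuals. Error rates obtained by applying log or root unconditionally say nothing about a transformation that an analyst would reject. For clipped-normal scores this stands: log and root make the residuals less normal there, so they would not qualify, and the large rates in that table cannot be charged to the rule. The reply fails for right-skewed scores, where these transformations do help normality and the artefact is large.

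Several stronger readings are tempting but not supported:

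- That rejection means SPADI will be transformed. The text equally allows a nonlinear mixed model, and software for such models can also fit bounded or non-normal likelihoods.
- That the test always rejects for trivial departures. At skewness 0.2 it does so in about a quarter to a third of runs. Clipping at 0 and 100 led to rejection in 18-78% of runs on marginal residuals but only 6-16% on conditional ones, and the article does not say which are tested.
- That every evolution finding is compromised. Only factors with a baseline difference are exposed. Sling wear is randomised, no baseline difference is expected, and its error rate stays near 5% on every scale examined.
- That the transformed answer is wrong in an absolute sense. It is false relative to SPADI points, the metric in which the protocol states its effect.

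An article may leave the residual type and the choice of transformation to a fuller plan, and their absence is not the point. The rule that is stated is.

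**Conclusion.** The point holds in a limited form. The protocol fixes a rule under which a significance test on about 500 residuals may take the primary analysis off the scale of its own effect size. The test often rejects for departures that did not disturb inference in points, and partly for a feature that the protocol anticipates. If the response is log or root and postoperative scores are right-skewed, a factor with a 10-point baseline difference and no effect on change is reported as a predictor of evolution in about 23-67% (root) or 47-94% (log) of trials, instead of about 5%.

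These rates rest on assumptions outside the documents: the shape and mean path of SPADI, the within-person correlation, the baseline difference and the transformation. With another distribution, or under the nonlinear-model branch, the artefact may be small or absent. The direction needs none of these figures, since the arithmetic for a 30-point fall shows it. It is worth correcting before analysis, but it does not invalidate the design.

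**What to change.** Replace the test-and-transform rule with wording to this effect: SPADI and SF-36 are analysed in points as the primary analysis whatever a normality test shows; residuals are examined by plots; if they are clearly non-normal, standard errors are empirical (sandwich) or come from a patient-level bootstrap. Any transformed, bounded-outcome or nonlinear model is a sensitivity analysis, with results back-transformed to points.

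The cost is one reworded paragraph. The article states that analyses follow completion of data collection, so the change should be recorded before they begin. The downside is slightly lower efficiency if the residuals prove strongly non-normal.
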